### Blinding

Due to the unique nature of the experimental treatment methods, implementing blinding posed challenges. In this study, grouping information will be concealed only from laboratory personnel, while clinical scales and statistical data will be collected and analyzed by dedicated staff. To strengthen methodological rigor, we have implemented full blinding for both outcome assessors (including NIHSS-certified raters) and statisticians throughout the trial process. This enhanced blinding strategy effectively prevents measurement bias that might arise from investigator anticipation or participant expectations, thereby improving the validity and objectivity of outcome evaluations.

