**Methods:**

Sixty-six patients with acute ischemic stroke will be randomly assigned 1:1 to control (conventional basal therapy, *n* = 33) and acupuncture (conventional standard stroke care + acupuncture, *n* = 33) groups for 10 days of intervention. The primary outcome is NIHSS score. The secondary outcomes: BMI and mRS scores, the level of TNF-A and IL-1B in serum, vascular endothelial growth factor (VEGF), Endocan ES, CD14+ and CD14- levels of peripheral blood mononuclear cells.

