### Study design

This is a randomized controlled trial with evaluator blinding to be conducted at the First Affiliated Hospital of Guangzhou University of Chinese Medicine. A total of 66 emergency inpatients will participate in this study. The experimental flowchart is shown in Figure 1. This study has received approval from the Ethics Committee of the First Affiliated Hospital of Guangzhou University of Traditional Chinese Medicine (Ethics Acceptance Number: JY2024-116).

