### Random allocation

A total of 66 patients were enrolled using simple randomization with a random number table and randomly assigned to the treatment group and the control group. The group assignments and treatment protocols were placed in opaque envelopes and kept by the attending physicians and acupuncture therapists, who administered the treatment according to the instructions in the envelopes.

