### Outcome measurement

Clinical indicators will be conducted uniformly by professional physicians or therapists. NIHSS scores will be assessed once before treatment (Day 1), during treatment (Day 5), and after treatment (Day 10). BMI and mRS scores will be assessed before treatment (Day 1) and after treatment (Day 10).

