### Data monitoring and statistical analysis

To minimize measurement bias arising from multiple evaluators, clinical indicator assessments and laboratory tests for each patient before, during, and after treatment will be conducted by the same specialized physician whenever possible. The physician evaluating the laboratory indicators will be blinded to the group assignments and treatment. To avoid missing or incorrect data, clinical and laboratory indicator evaluations will be conducted according to preset time points and entered into the electronic database promptly.

Data management and analysis will be performed using IBM SPSS Statistics Version 26 (IBM SPSS Inc., Chicago, United States). The principles of data processing are as follows: measurement data will be expressed as mean ± standard deviation (
$\bar{x}$
± S); if count data are normally distributed, the chi-square test will be used; if data in the two groups are normally distributed, t-test, repeated-measures analysis of variance (ANOVA), and multivariate linear regression will be used for comparative analyses; if count data are not normally distributed, the Mann–Whitney U test will be used; *p* < 0.05 will indicate statistically significant differences.

We will use the last observation carried forward (LOCF) method, which replaces missing data points with the patient’s last observed value. In order to provide a more comprehensive assessment of the treatment effects in this study, we will conduct both an intention-to-treat (ITT) analysis and a per-protocol (PP) analysis.

We will implement the Bonferroni correction during statistical analysis to rigorously control Type I error rates, thereby ensuring methodological stringency in accordance with your recommendation.

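### The Blinding section contradicts itself on whether NIHSS raters know the arm, so evaluator blinding of the primary outcome is not secured

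*Protocol article*

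**What the plan says.** The Study design section states: "This is a randomized controlled trial with evaluator blinding". The title says the same. According to the abstract, "The primary outcome is NIHSS score".

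The Blinding section then makes two statements, one directly after the other:

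- "grouping information will be concealed only from laboratory personnel", with the clinical scales and the statistics assigned to dedicated staff.
- "we have implemented full blinding for both outcome assessors (including NIHSS-certified raters) and statisticians throughout the trial process".

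It goes on to claim that this strategy prevents measurement bias arising from what investigators anticipate or what participants expect.

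Three other sections of the protocol article bear on who knows the arm and who rates:

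- Random allocation: group assignments are "placed in opaque envelopes and kept by the attending physicians and acupuncture therapists".
- Outcome measurement: "Clinical indicators will be conducted uniformly by professional physicians or therapists".
- Data monitoring and statistical analysis: "The physician evaluating the laboratory indicators will be blinded to the group assignments and treatment". Just before this, the section prefers that one specialised physician carry out a patient's assessments throughout, where possible.

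**The concern.** NIHSS, MBI and mRS all depend on a rater's judgement. The Interventions section compares basic treatment alone with basic treatment plus daily electroacupuncture, and it describes no sham. Patients and acupuncturists therefore know the arm, and a rater who does not know it is the main safeguard against detection bias in the primary outcome.

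The protocol article both asserts and denies that safeguard. Staff who followed the restrictive sentence would be complying with the text while scoring NIHSS in full knowledge of the allocation. The same conflict affects the statisticians, whom the second sentence blinds and the first does not.

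**Working it through.** The plan gives no figure on this point and no arithmetic applies. The check is a comparison of the sections.

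**1. Can the two sentences in Blinding both hold?** The first limits concealment to one group, the laboratory staff, and sets the clinical scales and the statistics apart as work for other, dedicated staff. The second adds two groups to the blinded set: outcome assessors, with NIHSS raters named, and statisticians. With the word "only" in place of any open-ended wording, the blinded set cannot be both laboratory staff alone and laboratory staff plus raters plus statisticians. One sentence must go.

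**2. Does another section decide which one?**

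| Section | What it fixes | What it leaves open |
|---|---|---|
| Title, Study design | Evaluators are blinded | Which evaluators: laboratory, clinical or both |
| Random allocation | Treating physicians and acupuncturists hold the assignments | Whether any of them also rates |
| Outcome measurement | Physicians or therapists score the clinical scales | Whether they are separate from treating staff |
| Main results | NIHSS assessors are trained, tested and checked by kappa | Whether they know the arm |
| Data monitoring and statistical analysis | The laboratory evaluator is blinded; the same physician is preferred throughout | The status of the clinical raters |

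None of them decides it. The training and kappa checks do not help, because kappa measures agreement: raters who all know the arm can agree well and still share a bias.

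**3. What follows under each sentence?** If the second governs, the evaluator-blinded label holds for NIHSS. If the first governs, blinding covers the laboratory measures (secondary outcomes) but not the primary outcome, and the label fails where it matters most.

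**4. The claim about participant expectations.** Blinding raters and statisticians limits what those people can add to a score. It does not change what a patient who knows the arm expects, reports or attempts during the examination. With no participant blinding and no sham described, the claim that such bias is prevented has no support.

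**The case against.** The strongest reply is that the intent is clear. The title, the Study design section and the more specific of the two blinding sentences all say that evaluators are blinded. Only one clause says otherwise. The second sentence is presented as an enhancement, and the final sentence of the analysis section answers somebody's recommendation, so the restrictive clause may be a leftover from before comments were addressed. This is plausible, and it makes an editorial slip more likely than a design without blinded rating. It remains an inference: the clause stands in the current text and nothing marks it as replaced.

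The objection does defeat several stronger readings that a reader might draw:

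- *The NIHSS raters are unblinded.* The document does not say so; it says two incompatible things.
- *The treating staff do the rating.* The job titles under Random allocation and Outcome measurement overlap, but the text never says they are the same people, and the Blinding section gives the scales to dedicated staff. Overlap is possible, not stated.
- *The analysis section confines blinding to the laboratory.* It mentions the laboratory evaluator and is silent on clinical raters. If one physician did both kinds of assessment for a patient, that physician would be blinded, so the section could even point the other way.

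A condensed article may also leave the practical means of keeping raters blind to the full protocol. That excuses missing procedure, but not two sentences that contradict each other.

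**Conclusion.** The concern holds as an internal contradiction on a point that protects the primary outcome. Evaluator blinding of NIHSS is not secured by the text, which is a narrower statement than saying that it is absent. The claim about participant expectations is a secondary overstatement.

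The size of any bias cannot be computed from the document. A reader might set one point of rater leniency against the planned difference of 12.61 − 7.53 = 5.08 and obtain 1 / 5.08, about 20%. The one point is arbitrary and nothing in the document supports it, so that percentage is no measure of the problem.

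The conclusion rests on two things: that the restrictive sentence is still in force as printed, and that the control arm has no sham, as the Interventions section describes it. The point should be corrected because both the trial's label and the main protection of its primary outcome depend on which sentence is followed.

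**What to change.** - **Blinding:** delete the clause confining concealment to laboratory personnel. State that NIHSS, MBI and mRS at every visit, including the 1- and 3-month follow-up, are scored by the trained dedicated assessors, who are blinded and are not the patient's attending physician or acupuncturist. Keep the statement that statisticians are blinded.
- **Blinding, last sentence:** remove the reference to participant expectations, and state that patients and therapists are not blinded.
- **Outcome measurement** and **Data monitoring and statistical analysis:** use the same description of the raters, and name clinical raters as well as the laboratory evaluator as blinded. The preference for the same physician throughout should give way where that physician knows the arm.
- **Random allocation:** make clear that those who hold the envelopes do not rate the same patients.

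Optional additions are hiding needle marks at assessment and recording the rater's guess of allocation. The correction does not depend on them.

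The cost is mainly wording, since the article already names dedicated staff and already plans assessor training. The small downside is some loss of rater continuity where the usual physician is unblinded. The sample size of 33 per group is unaffected.

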### Interventions

(1) Control group (conventional basic treatment): 33 patients

Standardized basic treatment will follow the “Chinese Guidelines for Stroke Prevention and Control” (2021 edition): ① Antiplatelet therapy: the use of antiplatelet aggregation drugs, including oral enteric-coated aspirin tablets (Bayer Medical and Health Co., Ltd., National Medical Approval No. J20171021) or oral clopidogrel bisulfate tablets (Lepu Pharmaceutical Co., Ltd., National Pharmaceutical Approval Letter H20123116); ② Lipid-regulating and plaque-stabilizing agents: oral atorvastatin calcium tablets (Beijing Jialin Pharmaceutical Co., Ltd., National Medical Approval No. H20093819). These medications will be administered continuously for 10 days. If patients have other underlying conditions, blood pressure, blood glucose levels, and water-electrolyte balance will be regulated based on individual circumstances.

(2) Acupuncture group (conventional basic therapy + acupuncture): 33 patients

① Basic treatment: Identical to that of the control group② Acupuncture treatment

Point Selection and Positioning: The DU meridian Baihui (DU20), Dazhui (DU14; Figure 2), and temporal three-needle are selected based on acupuncture and moxibustion (17) and Jin’s Three Needle Therapy (18). Baihui (DU20) acupoint positioning: Located 5 inches above the center of the head at the current hairline, or at the midpoint of the line connecting the tips of both ears. Dazhui (DU14) acupoint positioning: Located on the posterior midline, in the depression below the 7th cervical spinous process. Positioning of temporal three-needle: Temporal I needle: Located 2 inches above the hairline at the ear tip. Temporal II needle: 1 inch forward and laterally from Temporal I needle. Temporal III needle: 1 inch backward and laterally from Temporal I needle (Figure 3). Needles: Acupuncture needles, 1-inch in length, produced by Suzhou Tianxie Acupuncture Instrument Co., Ltd. (Production lot number: SuμRegistration 20,162,200,894)Attention: After acupuncture treatment, patients should apply pressure to the needle site to prevent subcutaneous bleeding and cleanliness. During the treatment period, patients should avoid consuming raw and cold fruits, shrimp, beef, mutton, and other similar foods.Course of Electroacupuncture: Needles will be retained for 30 min per session, once daily, for a continuous duration of 10 days.The acupuncture points of Du-14 (Dazhui), Du-20 (Baihui), and the temporal three-needle points will be connected to the positive and negative terminals of the G6805 electroacupuncture device (Qingdao Xinsheng Industrial Co., Ltd.). A dispersive-dense wave will be selected, with a frequency of 50 Hz and an intensity of 1 mA, and electroacupuncture treatment will be performed for 30 min. No manual needle manipulation will be performed during needle retention to eliminate inter-practitioner variability.

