### Blood serum index

In this study, enzyme-linked immunosorbent assay (ELISA) will quantify patients’ expression of inflammatory factors, including TNF-*α* and IL-1β (25), vascular endothelial growth factor (VEGF) (26), endothelial repressor ES (27),and peripheral blood mononuclear cells at pre-trial (Day 1), on-treatment (Day 5), and post-treatment (Day 10) levels. Additionally, flow cytometry will measure the CD14+ and CD14- levels of mononuclear cells in peripheral blood (28).

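### Minor, optional: the food restriction for the 10-day treatment period is written only into the acupuncture arm, so dietary advice goes with allocation at the Day 5 and Day 10 marker draws

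*Protocol article*

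**What the plan says.** The Methods paragraph of the abstract describes the experimental arm as "conventional standard stroke care + acupuncture" and the control arm as conventional therapy alone, with 33 patients planned in each.

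The Interventions section gives the detail. Control care follows a national stroke guideline and consists of an antiplatelet drug, atorvastatin, and management of other conditions as needed: "If patients have other underlying conditions, blood pressure, blood glucose levels, and water-electrolyte balance will be regulated based on individual circumstances". For the acupuncture arm, the first item reads "Basic treatment: Identical to that of the control group", and the second item is the acupuncture procedure.

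Within that second item, a note headed Attention contains two instructions. The first is needle-site care: "After acupuncture treatment, patients should apply pressure to the needle site to prevent subcutaneous bleeding and cleanliness". The second, immediately after it, is the food restriction: "During the treatment period, patients should avoid consuming raw and cold fruits, shrimp, beef, mutton, and other similar foods". Sessions are given "once daily, for a continuous duration of 10 days".

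The Blood serum index section schedules the ELISA markers "at pre-trial (Day 1), on-treatment (Day 5), and post-treatment (Day 10) levels". The Discussion states the mechanistic aim in terms of acupuncture itself: whether it raises CD14+ and CD14- cells, with the inflammatory and vascular markers as serological indicators.

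**The concern.** Basic treatment is declared equal, so whatever stands under the acupuncture item is the written difference between the arms. That item holds a dietary instruction as well as needling and electrical stimulation. The abstract and the Discussion present the difference as acupuncture.

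The mechanistic outcomes are what is at stake. If the acupuncture arm shows a different marker profile at Day 5 or Day 10, a reader can ask whether the advice contributed. The trial cannot answer, because everyone allocated to acupuncture is given the advice and, on the written text, nobody allocated to control is. A diet effect, if there is one, could resemble an acupuncture effect or offset it. A statistical analysis plan could not repair this, since no analysis can separate two instructions that always occur together.

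**Working it through.** The plan gives no figure on this point, so the check is a comparison of the texts.

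1. **Where the restriction appears.** It occurs once in the article, in the Attention note of the acupuncture procedure. The neighbouring instruction concerns pressure on the needle site and can apply only to needled patients, so the note is naturally read as addressed to that arm.

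2. **What controls are told.** The control-arm paragraph lists antiplatelet therapy, a statin, and individual regulation of blood pressure, glucose and water-electrolyte balance. It has no food advice, and no other section gives any to controls.

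3. **What is shared.** Basic treatment is identical by statement. The restriction is outside basic treatment, so that statement does not extend it to controls. It is not contradicted either: the two arms can have the same basic treatment and still differ in this advice.

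4. **Timing.** The restriction applies during the treatment period, which is 10 days of daily sessions. Setting the draws against that period:

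| Draw | Position relative to the advice |
|---|---|
| Day 1 | Before treatment |
| Day 5 | During the period |
| Day 10 | At the end of the period |

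   Both post-baseline draws, 2 of 3, are covered. The Day 1/5/10 schedule is stated for the ELISA markers and mononuclear cells. The flow cytometry sentence on CD14+ and CD14- cells gives no separate schedule, so I assume the same days.

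5. **Which outcomes.** The markers are secondary. The primary outcome is the NIHSS score.

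6. **Size of any effect.** No section links these foods to TNF-α, IL-1β, VEGF, ES or CD14 cells over 10 days, and no section gives an expected acupuncture effect on these markers. The planning difference in the Sample size section is for NIHSS and cannot be carried over. Neither the size nor the direction of a diet effect can be derived, so no false-positive rate or loss of power is calculated.

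7. **Effect on sample size.** The planned number is calculated from NIHSS: 2 × (1.96 + 1.28)² × 5.62² / 5.08² = 25.7, rounded up to 26 per arm. Allowing for 20% dropout, 26 / 0.8 = 32.5, rounded up to 33 per arm and 66 in total. None of these inputs depends on the dietary advice, so correcting the sentence leaves the number unchanged.

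**The case against.** The strongest reply is that nothing here is an error. An add-on trial against usual care ordinarily compares a package, and precautions that accompany needling belong to it. On that reading the randomised comparison is sound. This stands: the comparison of acupuncture plus its advice with usual care is valid. It does not fully answer the point, because the abstract names the added element as acupuncture and the Discussion asks what acupuncture does to the markers.

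A second reply is that the real contrast may be absent. The patients are inpatients and ward meals may govern intake in both arms. The guideline behind control care is not shown. The wording refers to patients in general, and the article condenses a fuller protocol. All of this is possible and limits the size of the point. It does not make the written text balanced, and if both arms were meant, the same edit makes that clear.

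A third reply is that, without a sham arm, daily therapist contact and expectation also go with allocation, so balancing one sentence does not make marker changes attributable to needling. That is correct. The edit removes one avoidable alternative explanation and leaves the others.

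A reader might infer that the marker results are confounded by diet, or that the NIHSS comparison, the blinding or the randomisation is damaged. The documents do not support this. They show a difference in written instructions, not in what patients eat, and no effect of these foods on any outcome.

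**Conclusion.** The point holds as a minor, optional improvement. As written, a dietary instruction goes with allocation over the 10 days, and the Day 5 and Day 10 comparisons of the secondary markers cannot separate it from acupuncture. This rests on reading the Attention note as addressed to the acupuncture arm only, which its position and the preceding needle-site instruction support, and on the assumption that CD14+ and CD14- cells are measured on the same days as the ELISA markers.

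The size of any consequence is unknown and may be nil, and actual diet may be the same in both arms. It would be tempting to attach a range of assumed diet shifts and report the resulting error rates, but the documents offer nothing to anchor either the shift or the true marker effect, and such figures would say nothing about diet.

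**What to change.** Move the food sentence out of the Attention note and into the basic treatment as an item for both groups, for example: Dietary advice (both groups): for the 10 days of treatment, avoid raw and cold fruit, shrimp, beef, mutton and similar foods. The needle-site instruction stays where it is.

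The cost is one amended sentence and one extra piece of dietary advice for controls. No additional patients, visits or staff are needed.

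There is one further downside. The Random allocation section is written in the past tense, so recruitment may already have begun. If it has, controls enrolled before and after the amendment would receive different advice. The amendment date should then be recorded. If the sponsor prefers not to change the advice mid-trial, the intervention should be described as acupuncture with accompanying dietary advice and the mechanistic conclusions worded to match. Under either course, the lack of a sham arm still limits attribution to needling.
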